**Methods:**

The Dynamic Adaptation Process will be used first to inform the adaptation and implementation of OTCH to the Chilean context. Then, a Hybrid Type 1 trial design will test its effectiveness and cost and evaluate its implementation using a cluster-randomized controlled trial (RCT) (*N* = 300 from 21 outpatient clinics). The OTCH program will be offered in half of these outpatient clinics to individuals ages 15-35. Usual care services will continue to be offered at the other clinics. Given the current COVID-19 pandemic, most research and intervention procedures will be conducted remotely. The study will engage participants over the course of 2 years, with assessments administered at enrollment, 12 months, and 24 months. Primary outcomes include implementation (fidelity, acceptability, and uptake) and service outcomes (person-centeredness, adherence, and retention). Secondary outcomes comprise participant-level outcomes such as symptoms, functioning, and recovery orientation. Over the course of the study, interviews and focus groups with stakeholders will be conducted to better understand the implementation of OTCH.

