## Methods/design

### Study design

This effectiveness-implementation Hybrid Type 1 trial aims to examine both the implementation and effectiveness of OTCH. A Hybrid Type 1 design, as we propose, tests the effects of a clinical intervention on client-level outcomes, while at the same time exploring multi-level implementation factors that can inform and promote the use of the intervention in real-world settings. It has been proposed as a solution to accelerate the process of transferring evidence-based practices into usual care. Moreover, the Dynamic Adaptation Process (DAP) [14] will be used to adapt and implement OTCH, as well as to examine fidelity and document implementation barriers and facilitators. The DAP provides a way to thoroughly identify and incorporate adaptations at multiple levels and facilitate implementation across the whole study. In contrast to most dissemination and implementation models, within the DAP, modifications, and adaptations are made by a team exclusively devoted to this task known as “Research Adaptation Team,” who is composed of multiple stakeholders and aimed to reflect what was learned about: a) understanding contextual conditions, and how context might be modified; and b) how these conditions might modify the nature of the content of the intervention curriculum.

A cluster-RCT will be conducted among 300 participants with FEP drawn from 21 outpatient clinics that include marginalized and poor communities to test the effectiveness of OTCH (see Fig. 1 below based on PRISMA guidelines).

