### Randomization

The 21 participating clinics will first be divided into two groups based on the poverty level of the catchment area and expected enrollment of individuals with FEP for each clinic. The largest site will be matched with two clinics of a similar poverty level and clinic size as well, as noted above. The matching will be done based on a visual inspection of a scatter plot of expected enrollment by the income of each site. Then, blocks of size 2, and one block of size 3, will be randomly generated. Randomization will be performed using a randomization scheme generated by SAS 9.4. This procedure will entail (1) generating a random number 0 or 1 ten times, and (2) assigning 0 to the Usual FEP care clinic and 1 to the OTCH clinic in each matched pair. For the block of size 3, two sites will be assigned to either OTCH or Usual FEP care, and the remaining site to either OTCH or Usual FEP care as well. The statistician will notify the contact-PI once the randomization is done, and he will then call the CMHC Director to inform him/her of the assigned treatment status, followed by a written note to the Director with the same information. The random allocation within blocks of two will enable us to bring into the study one OTCH and one Usual FEP Care CMHC per month. We note that the randomization (and notification) will be done at the start of the project, which will enable us to select equal numbers of OTCH and Usual FEP Care CMHCs for data collection (at organizational, provider, and participant level) during the preparatory phase.

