#### Aim 1a and Aim 1b analyses

We have selected 3 measures of implementation (fidelity, acceptability, and uptake) and 3 measures of service outcomes (patient-centeredness, adherence, and retention) that represent the active ingredients of CSC for people with FEP. These six measures reflect care processes that will be fundamental to the implementation of the OTCH program [13]. Tests for treatment differences between the intervention arms on each of the six outcomes will be performed using a hierarchical linear model (HLM) for each outcome including clinic-level random effects to account for clustering of participants within clinics and participant-level random effects to account for repeated measures on the same user over time. The primary fixed effects will be an indicator for intervention status (OTCH, FEP Usual Care), time (12 or 24 months), and intervention*time. The magnitude and statistical significance of the beta coefficients from the HLMs will be used to test whether implementation and service outcomes differ between intervention arms at 12 and 24 months. If descriptive analyses identify any baseline differences between randomized groups of participants at baseline, we will consider adding the respective covariate to the model to adjust for this.

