We will examine multilevel factors that may moderate the implementation of OTCH (see Table 1). (1) *Community level*: there is evidence that access to and engagement with mental health services is low among those who reside in poor communities [41]. (2) *Provider level*: we hypothesize that more positive attitudes toward evidence-based practices and recovery orientation will be associated with more successful implementation of programs which have these characteristics like OTCH [42]. (3) *Participant level*: we also hypothesize that socio-demographics and baseline clinical state will be predictors of implementation and service outcomes based on prior studies with clinical outcomes [17]. We will test this aim by including all three types of moderators into the HLM utilized for Aim 1.a. Specifically, because we aim to test whether these factors differentially affect the implementation of the OTCH compared to FEP usual care (i.e., an interaction with treatment), we will incorporate a random intervention effect into the HLM and allow the factors to predict the random intervention effect at both the clinic and participant level. The magnitude and statistical significance of the beta coefficients for these factors will provide the test of them as treatment effect moderators.

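### The Aim 1b moderator model includes a random intervention effect whose variance this design cannot identify, because every clinic and participant is in one arm only

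*Protocol article*

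**What the plan says.** The protocol article (Study design) states that a "cluster-RCT will be conducted among 300 participants with FEP drawn from 21 outpatient clinics". Under Randomization, the allocation step is "assigning 0 to the Usual FEP care clinic and 1 to the OTCH clinic in each matched pair", with one further block of three clinics. The abstract adds: "Usual care services will continue to be offered at the other clinics". No crossover or stepped roll-out is described.

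The Aim 1a model is a hierarchical linear model (HLM) "including clinic-level random effects to account for clustering of participants within clinics and participant-level random effects to account for repeated measures". Its main fixed effects are intervention, "time (12 or 24 months), and intervention*time". The matched block is not a level of this model.

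Aim 1b is to be tested by "including all three types of moderators into the HLM utilized for Aim 1.a". Because the target is an interaction with treatment, the plan adds "a random intervention effect into the HLM and allow the factors to predict the random intervention effect at both the clinic and participant level". Its test is then stated: "The magnitude and statistical significance of the beta coefficients for these factors will provide the test of them as treatment effect moderators".

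**The concern.** A random intervention effect describes how the difference between OTCH and usual care varies from unit to unit. A unit informs that variation only if it is seen under both conditions, as in a multisite trial that randomises within site. Here arm is constant within a clinic, within a participant and over time. The stated HLM therefore has no level across which the added random effect can be learned.

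Aim 1b is a stated research objective, and the article commits to this model rather than leaving it open. An analyst who fits it as written may get a singular or non-unique solution and would then have to choose another specification with the data in view. A published estimate of how much the OTCH effect varies between clinics or participants would carry no information about that question.

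**Working it through.** **Inputs.** 21 clinics, each in one arm (Study design; Randomization); random effects for clinic and participant (Aim 1a analysis); two post-baseline times, 12 and 24 months (same place); intra-class correlation 0.05 (Sample size and power analysis), used only for illustration. The plan gives no figure to reproduce; the question is one of identifiability.

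**Model as written.** Let A be the arm of the clinic (0 usual care, 1 OTCH). At clinic level write τ00 for the intercept variance, τ11 for the intervention-slope variance and τ01 for their covariance. Write ω00, ω11 and ω01 for the same at participant level, and σ² for the residual variance.

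**What the data determine.**
- Covariance between two participants of one clinic: τ00 if A = 0; τ00 + 2τ01 + τ11 if A = 1.
- Additional covariance between two times in one participant: ω00 if A = 0; ω00 + 2ω01 + ω11 if A = 1.
- Additional variance of a single observation: σ².

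That is 2 + 2 + 1 = 5 estimable quantities for 3 + 3 + 1 = 7 parameters.

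**Numerical check.** The rank of the derivatives of the marginal covariance matrix with respect to the variance parameters, for 21 one-arm clinics, participants nested in clinics and two times:

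| Random effects (plus residual) | Parameters | Rank |
|---|---|---|
| Clinic and participant intercepts only | 3 | 3 |
| Clinic intercept, covariance, slope; participant intercept | 5 | 4 |
| Intercept, covariance, slope at both levels | 7 | 5 |
| Intercept and slope at both levels, covariances zero | 5 | 5 |

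**Illustration.** Take total variance 1 and clinic variance 0.05. The OTCH clinic variance τ00 + 2τ01 + τ11 is then:
- (τ00, τ01, τ11) = (0.05, 0, 0): 0.05
- (0.05, −0.02, 0.04): 0.05 − 0.04 + 0.04 = 0.05
- (0.05, −0.04, 0.08): 0.05 − 0.08 + 0.08 = 0.05
- (0.05, −0.05, 0.10): 0.05 − 0.10 + 0.10 = 0.05

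The usual-care variance is 0.05 in every row. Slope variances from 0 to 0.10 therefore have the same likelihood.

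**Zero covariance.** The OTCH variance becomes τ00 + τ11, so τ11 = OTCH variance − usual-care variance. It measures unequal spread between arms, not variation of the treatment effect. Kept non-negative, it also forces the OTCH variance to be at least as large as the usual-care variance.

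**Effect on the moderator tests.** The generalised least-squares covariance of the coefficients is (X′V⁻¹X)⁻¹. It depends on the variance parameters only through V, and V is constant along the flat ridge. In a layout of 21 clinics, 13 participants each and two times, four points on the ridge gave the same standard errors: 0.15557 for arm, 0.25706 for arm by clinic moderator and 0.11054 for arm by participant moderator. Only the equality matters, since the moderator values were artificial.

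**Without the random intervention effect.** A fixed part with intercept, arm, time, arm by time, one clinic moderator, one participant moderator and both arm-by-moderator products has 8 columns and rank 8. The moderation tests are therefore estimable. For one clinic-level moderator the clinic-level coefficients are intercept, arm, moderator and their product, which leaves 21 − 4 = 17 degrees of freedom.

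**The case against.** The strongest reply is that the article defines its test as the coefficients of the moderators, and that letting factors predict the intervention effect is ordinary multilevel phrasing that reduces to fixed interaction terms. This stands: the aim is testable and those coefficients are sound. It does not remove the random effect that the text explicitly adds.

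A second reply is that the article specifies no intercept-slope covariance, that the zero-covariance model is identified, and that covariance structure is detail for the analysis plan. The first two parts are right. But that version answers a different question, so no choice of covariance gives the added term its stated meaning. Reading the closing phrase about clinic and participant level as describing the factors does not help either: arm still varies at no level of the stated HLM.

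Stronger readings are tempting and are not supported:
- A reader might infer that the model is bound not to converge. What follows is only that no unique solution exists when the covariance is included; software may still return one of many.
- A reader might infer that the moderator standard errors are unreliable. They are unchanged along the ridge. The zero-covariance version could affect them if the OTCH variance is in fact the smaller.
- A reader might multiply the moderators in Table 4 by the six outcomes to count expected false positives. Table 4 does not allow it: acceptability is measured on providers only, fidelity draws on provider feedback, supervision calls and site visits, and uptake has several instruments.
- A reader might move the random effect to the matched block, where both arms occur. With pairs alone and clinic intercepts kept, that model is also unidentified (6 parameters, rank 5). Only the single block of three raises the rank to 6, so the estimate would hang on one block.

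**Conclusion.** The point holds, at moderate severity. As written, Aim 1b specifies a random intervention effect that the design cannot support: two of seven variance parameters are unidentified when it is placed at both levels with covariances, and one of five when it is placed at clinic level only. With covariances at zero the term can be estimated but is mislabelled. The conclusion rests on arm being fixed per clinic for the whole trial, analysis by allocated arm, and an HLM with clinic and participant as its only random levels, all of which the article states or implies. It does not undermine the Aim 1a comparison or the moderator coefficients. The exposure is an unstable or non-unique fit, a model chosen after the data are seen, and a reported effect variance that cannot be interpreted.

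**What to change.** Reword the Aim 1b model as follows:
- Remove the random intervention effect at both levels.
- Keep random intercepts for clinic and participant. If unequal spread between arms is expected, allow arm-specific variances and describe them as such.
- Test each moderator by a fixed intervention-by-moderator term.
- For clinic-level moderators such as catchment poverty, use between-clinic degrees of freedom: about 17 with one moderator in the model.

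The cost is a few sentences of analysis text, and the model becomes simpler. Data collection, sample size and randomisation are untouched. The change should be dated before outcome data are examined by arm, so that it is not a response to a failed fit.

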For the cluster trial, power was calculated conservatively based on the participation of 270 participants (rather than the full 300 to be enrolled), anticipating a possible participant drop-out of ~10%. We estimated that, with at least 10 clinics in each condition, we will have 80% power to detect a difference in mean outcomes between study conditions with a moderate effect size of Cohen’s *d* = 0.35 following the standard detectible effect size formula for clustered randomized trials [15, 16]. This power calculation was derived assuming an intra-class correlation of 0.05 for outcomes by clinic (15 participants nested within 21 clinics). We also assume an alpha of 0.05 and that all tests are 2-tailed. Previous research has shown interventions like OTCH to have moderate to large effects on implementation and service outcomes, such as medication adherence, service utilization, and engagement in treatment [5, 17]. We have also shown that FEP providers in Chile rely primarily upon medication and are usually not trained to promote shared decision-making, recovery orientation, or person-centered care [9]. Then it is reasonable to anticipate at least moderate (and probably large) effects of OTCH on these indicators of implementation. Finally, evidence for the expected effect on participant-level symptoms and functioning comes from the RAISE Connection Program study, which indicated improvement over 24 months for participants enrolled (e.g., PANSS improvement effect size 0.91, occupational functioning 1.2, and social functioning 0.72) [17]. Power to detect mediation effects (Aim 2b) depends on the size of the effect of intervention on implementation and service outcomes (path a), and the correlation between implementation and services outcomes and participant level symptoms, functioning, and recovery (path b). Based on tabulated recommendations for sample sizes needed to test mediation effects with a sample of size *N*=270 with follow-up data, we have over 80% power to detect a significant mediation effect with path a=.26 and b=.26. Path a is expected to be >0.35 (argued for Aim 1 above), and we expect based on our previous work that there will be at least moderate associations between implementation and clinical outcomes (*r*>0.40), assuming no confounding of mediator-outcome relationship.

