Clinical outcomes	Psychotic symptoms	Participants	*Positive and Negative Syndrome Scale (PANSS)* [28] scale will be used to assess positive and negative symptoms (only the first 14 items). This scale includes seven rating points that represent increasing levels of psychopathology, from 1 (“absent”) to 7 (“extreme”). Range *7–*49 points.	Baseline, 12, 24 months	20 min
	Functioning	Participants	The *Social and Role Functioning in Psychosis and Schizophrenia* (SRFP) [29] scale asks for social, behavioral, and occupational difficulties associated with mental illness, including psychosis and schizophrenia. The scale rates functioning on a scale of 0 (“extreme role dysfunction”) to 10 (“superior social/interpersonal functioning”). Range: 7–70 points.	Baseline, 12, 24 months	20 min
	Recovery orientation	Participants	The *Questionnaire about the Process of Recovery (QPR)* [30] assesses users’ perceptions about recovery from psychosis. It has 15 items each scored on a 4-point scale ranging from 0 (“strongly disagree”) to 4 (“strongly agree”). Higher scores on the measure are indicative of recovery (Range: 0–60 points).	Baseline, 12, 24 months	15 min
Moderators	Poverty	Community-level	Administrative data from the *Chilean System of Social Protection* [31] will be utilized to estimate percentage of the population living below the national poverty lines (0–100%).	As available across study period	N/A
	Providers’ Attitudes to EBP	Providers	This will be measured by the *Evidence-Based Practice Attitude Scale* (EBPAS) [21] as described above under implementation outcomes.	Baseline	10 min
	Providers’ Recovery orientation	Providers	The *Recovery Self-Assessment (RSA)* [24] as described above under implementation outcomes	Baseline	15 min
	Symptoms	Participants	Measured by PANSS [28] as described above under clinical outcomes	Baseline	20 min
	DUP	Participants	The time between the onset of psychotic symptoms and initiation of treatment at a mental health clinic based on the FEP registry.	Baseline	NA
	Functioning	Participants	Measured by *SRFP* [29] as described above under clinical outcomes	Baseline	20 min
	Socio-demographics	Participants	Age (15–19, 20–24, 25–29, 30–34, 35–40 years), gender (male, female), ethnicity, education, employment, and marital status	Baseline	10 min

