**Fig. 3 Fig3:**
[figure not shown]
Conceptual model for analysis

We will carry out all analyses on an Intention-to-treat basis. All tests will be two-sided with critical value *α*=0.05. Prior to analysis, we will examine all variables for outliers and inconsistencies and examine their distributions. The distributions of all continuous variables will be checked for normality, and transformations will be employed to normalize distributions, if necessary, before applying specific parametric techniques. Missing data will be imputed, using multiple imputation procedures in standard statistical software (e.g., Stata or SAS).

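### Aim 1b tests roughly 34 to 72 moderator-by-outcome interactions at 0.05 with no priority order, adjustment or exploratory label, so a chance moderator is likely to very likely

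*Protocol article*

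**What the plan says.** In the Data analysis section of the protocol article, the level is set once for everything: "All tests will be two-sided with critical value *α*=0.05". The power section repeats it: "We also assume an alpha of 0.05 and that all tests are 2-tailed".

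Under Aim 1a and Aim 1b analyses, one model is fitted per outcome: "Tests for treatment differences between the intervention arms on each of the six outcomes will be performed using a hierarchical linear model (HLM"). The six outcomes are fidelity, acceptability, uptake, patient-centeredness, adherence and retention. For moderation the same section continues: "We will test this aim by including all three types of moderators into the HLM utilized for Aim 1.a". The decision rule is then: "The magnitude and statistical significance of the beta coefficients for these factors will provide the test of them as treatment effect moderators".

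Table 4 has seven moderator rows:
- one at community level: poverty, from administrative data that "will be utilized to estimate percentage of the population living below the national poverty lines";
- two at provider level: attitudes to evidence-based practice and recovery orientation;
- four at participant level: symptoms, duration of untreated psychosis (DUP), functioning and socio-demographics.

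The socio-demographic row holds six variables: age band, gender, and "ethnicity, education, employment, and marital status". Split out, the table gives 12 variables.

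Moderation is a named part of Aim 1 in the Research objectives. The article states no priority order, multiplicity adjustment or exploratory status for these tests. Its power calculations cover the two-arm comparison and the mediation effects, not interactions.

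**The concern.** A rule that applies 0.05 separately to each of several dozen interactions leaves the error rate of Aim 1b as a whole uncontrolled. Even if OTCH worked equally well in every community, with every kind of provider and for every client, the rule would probably name some factor as a moderator.

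The stake is practical. The abstract and the Discussion say that what is learned about facilitators and barriers should inform expansion of these services in Latin America. A chance interaction with poverty, ethnicity or provider attitudes, reported as having passed the protocol's own test of moderation, could steer decisions on where and for whom the programme is offered.

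**Working it through.** The article states no error rate or power for the moderator tests, so there is no figure of its own to reproduce. The check applies the stated rule to the stated lists.

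**Inputs from the article**
- Level: two-sided 0.05 for every test (Data analysis).
- Outcomes: 6 (Aim 1a and Aim 1b analyses).
- Moderators: 7 rows or 12 variables (Table 4). Three are at community or provider level; the rest are 4 rows or 9 variables at participant level.

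**Inputs assumed**
- No factor truly moderates any outcome.
- One test per moderator and outcome.
- Correlation among test statistics: the article gives none, so a range is shown.

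**Step 1: number of tests.** Fidelity is rated from provider feedback, supervision calls and site visits, and acceptability is the providers' own attitude score. A client's age or DUP does not attach naturally to either. If participant-level factors are tested only on the other four outcomes:
- 12 variables, all pairs: 12 × 6 = 72
- 12 variables, feasible pairs: 3 × 6 + 9 × 4 = 54
- 7 rows, all pairs: 7 × 6 = 42
- 7 rows, feasible pairs: 3 × 6 + 4 × 4 = 34

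Reading 12 and 24 months separately doubles each count (72 becomes 144). Splitting uptake into its several instruments also raises it.

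**Step 2: expected false moderators.** This is k × 0.05, whatever the correlation: 34 × 0.05 = 1.7 and 72 × 0.05 = 3.6.

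**Step 3: chance of at least one.** Under independence it is 1 − 0.95^k. For tests that all share correlation 0.5, it is the probability that at least one of k equicorrelated normal statistics exceeds 1.96 in absolute value. The third column takes moderators as independent and lets only the outcomes correlate. At outcome correlation 0.5, one moderator has a false-positive chance of 0.207 over six outcomes and 0.156 over four; for example, 72 tests give 1 − (1 − 0.207)^12 = 0.938.

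| Tests | Expected false | All equicorrelated 0.5 | Outcomes correlated 0.5, moderators independent | Independent |
|---|---|---|---|---|
| 34 | 1.7 | 53% | 75% | 82.5% |
| 42 | 2.1 | 58% | 80% | 88.4% |
| 54 | 2.7 | 64% | 89% | 93.7% |
| 72 | 3.6 | 71% | 94% | 97.5% |

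Raising the outcome correlation to 0.8, with moderators still independent, gives 61% for 34 tests and 83% for 72.

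**The case against.** The best defence is that this is a journal article. Ordering and multiplicity control for a moderator sub-aim are commonly left to the analysis plan, and a general 0.05 does not forbid later ordering. That would answer a complaint about silence. Here the article does set a rule: a level for all tests, and significance, together with magnitude, as the test of moderation. An analysis plan that relabelled these tests would depart from the published rule. Magnitude is part of the rule, but the article gives no threshold for it, so it does not limit the error rate.

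Three stronger readings are tempting, and the article does not support them.

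- **That the moderator claims are confirmatory.** The section opens by saying that factors which might moderate will be examined, and the Study design section describes Hybrid Type 1 trials in general as exploring implementation factors. The participant-level hypothesis concerns prediction of outcomes, not moderation in a stated direction, and no explicit hypothesis is given at community level. The wording is mixed: language of examining sits beside a rule that delivers a test. The fair description is that the status is not stated.
- **That there are at least 72 tests.** Seventy-two needs the socio-demographic row split into six and client characteristics tested against fidelity and provider acceptability. Without those steps the count falls to 34. Two visits, five age bands or separate uptake instruments would raise it, so the article fixes no single number.
- **That a false claim is almost certain.** That holds only for the larger counts with near-independent tests. With all tests equicorrelated at 0.5, the chance is 53% to 71%.

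**Conclusion.** The concern holds in moderate form. As written, Aim 1b applies a significance rule at 0.05 to roughly 34 to 72 interactions without order, adjustment or exploratory label. If no factor moderates, 1.7 to 3.6 false moderators are expected. At least one is likely to very likely: about 53% to 71% with all tests equicorrelated at 0.5, and 82.5% to 97.5% under independence. Every figure is conditional on no true moderation and on correlations that the article does not give. Across the counts and correlations tabulated, the chance is at least ten times the nominal 5%.

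The severity is modest. Aim 1b is a sub-aim, and the main comparison of OTCH with usual care, the sample size and the power claim do not depend on it. What changes is how firmly a moderator finding may be stated.

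**What to change.** In the Aim 1b text, replace the sentence that makes significance the test of moderation with a statement that these interactions are hypothesis-generating and will be reported as estimates with 95% confidence intervals.

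If a confirmatory moderator claim is wanted, name a small set in advance, for example one moderator per level, at one time point. Apply Holm across every moderator-by-outcome test in that set, not only across the moderators, and leave the rest exploratory. Three moderators on six outcomes make 3 × 6 = 18 tests, so the smallest p-value would be compared with 0.05 / 18 = 0.0028. Naming fewer outcomes as well would ease that threshold.

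The first option costs wording only. Neither option changes data collection, sample size or conduct. The price is that a moderator can no longer be claimed on p < 0.05 alone.
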